## 2. Materials and Methods

### 2.1. Ethical Approval

The study protocol was registered and approved by the Bioethics Committee of the Faculty of Medical Sciences, University of Warmia and Mazury in Olsztyn on 17 June 2010 and 25 April 2019, Resolution No. 20/2010 and Resolution No 43/2019). Written informed consent to participate was obtained.

### 2.2. Participants Selections

The participants will be recruited for the study through ads in the press, via the Internet and by e-mail invitation between October and December 2019. Approximately 140 women with HT are expected to respond to the invitation letter (describing the details of the planned trial) and will be screened for eligibility (Figure 1). All visits for data collection will take place at the Department of Human Nutrition (Center of Gastronomy with Dietetics and Food Bioassessment), Faculty of Food Science, University of Warmia and Mazury in Olsztyn. The trial starts in winter months, and all subjects will be advised to continue their long-term vitamin D supplementation. 

To take part in the study, the participants have to be prior diagnosed as having HT according to the American Thyroid Association guidelines [26] and have a medical certificate for levothyroxine or other thyroid hormone treatment (e.g., levothyroxine plus liothyronine). The participants will be required to show a medical diagnosis with thyroid ultrasonography and the results of thyroid function tests carried out no later than two months before enrolment. Detailed inclusion and exclusion criteria are presented in Table 2. Information collected at the interview, which not will be used as including/excluding criterion, is the age at which HT was diagnosed, the use of dietary supplements in the past, the dose of levothyroxine or other thyroid hormones in current treatment, and hormone status (menstruating: yes, no, irregular). Elevated serum auto-antibodies against thyroid peroxidase and thyroglobulin will be recorded but will not be used as excluding criterion.

### 2.3. Randomization and Blinding

Patients will be randomly allocated to either the experimental group (QDP; approximately n = 50) or the control group (CDC; approximately n = 50). Stratified randomization will be based on age and will be carried out by a researcher not directly involved in the study. The patients will be unaware of whether they belong to the experimental or the control group. The researchers and laboratory personnel who will be involved in data collection and measurements (excluding the researcher who will be involved in dietetic counseling) will not know if a participant is included in the QDP group or the CDC group. The study is designed as a single-blinded study without a placebo.

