## Abstract

The current state of knowledge related to diet in Hashimoto thyroiditis (HT) is far from satisfactory, as many HT subjects experience several disorders and report reduced quality of life. There are three aims of the study: (1) to develop a qualitative dietary protocol (QDP; ‘Diet4Hashi’) as a simple, graphic–text tool dedicated to TH subjects, (2) to evaluate the use of the QDP in dietetic counseling compared to conventional dietetic counseling (CDC) in HT women, and (3) to assess the impact of both the QDP and the CDC on the diet quality, quality of life, adiposity, and metabolic parameters of HT women. The QDP is based on subject self-monitoring supported with a graphic–text tool to help them in food selection and adequate food frequency consumption, while the CDC on oral explanation and printed sample menus were provided by a dietician. The QDP contains two lists: (A) foods recommended for consumption and (B) foods with limited consumption, along with indicated consumption frequency per day/week/month. Both approaches include the same dietary recommendations for HT extracted from the literature but differ in subject–dietician cooperation. To summarize the evidence regarding dietary recommendations in HT, the PubMed, Embase, and Cochrane Library databases (to March 2019) and the bibliographies of key articles were searched. The study is designed as a dietary intervention lasting six months in two parallel groups: experimental and control. In the experimental group, the QDP will be applied, while in the control group, the CDC will be applied. In total, the study will include a baseline of 100 women with diagnosed HT. The subjects will be randomly allocated into the experimental/control groups (50/50). Data related to diet quality and other lifestyle factors, nutrition knowledge, quality of life, thyroid function, body composition, blood pressure, serum fasting glucose, and lipid profile at baseline and after a six-month follow-up will be collected. This study was conducted to develop a dietary protocol (Diet4Hashi) that is easy to follow for HT subjects, and it will contribute to providing valuable data that are useful to dieticians and physicians. It is anticipated that this graphic–text qualitative dietary protocol, by improving food selection and diet quality, may reduce adiposity and improve metabolic parameters and the quality of life of HT women.

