### 2.11. Sample Size

The minimum sample size was calculated based on the expected improvement in overall QoL (decrease in points) and BMI (decrease in kg/m^2^) after the six-month follow-up and the expected difference between the experimental and the control group. A decrease in overall QoL and BMI with a 50% difference between groups (in the experimental/control group, a decrease by 20/10 points and 2.0/1.0 kg/m^2^, respectively) was assumed. For this calculation, a 5% significance level and 80% power were considered. The sample size required at baseline is approximately 100 respondents (for the experimental/control group: 50/50 for overall QoL and 42/42 for BMI), including a 20% drop-out rate at the end of the study. When the data collection is completed, the adequacy of the study sample will be checked by applying the post hoc statistics to calculate power.

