### 2.12. Statistical Analysis

Categorical variables will be presented as a sample percentage (%) and continuous variables will be presented as means with a 95% confidence interval (95%CI) or medians with an interquartile range (IQR) for variables with normal or non-normal distribution, respectively. To assess the impact of dietetic counseling and verify the differences between the experimental and the control group, two-tailed tests will be applied; *p*-values < 0.05 will be considered significant. 

The normality of variable distribution will be verified with a Kolmogorov–Smirnov test before the statistical analysis. For continuous variables, e.g., diet quality scores, AdhS, scores of QoL, nutrition knowledge score, TFTs, markers of adiposity, metabolic parameters, and changes after a six-month follow-up with respect to baseline will be verified with a T-test for dependent samples or a Mann–Whitney test, for variables with normal or non-normal distribution, respectively. For categorical variables, logistic regression modeling will be applied to determine the chance of the occurrence of high diet quality, high AdhS, high QoL, as well as low adiposity and elevated metabolic parameters. The odds ratios (ORs) and 95% confidence intervals (CIs) will be calculated. The significance of ORs will be verified with Wald’s statistics. A crude model and models with an adjustment for confounders will be created. All analyses will be performed with Statistica software (version 13.3 PL; StatSoft Inc., Tulsa, OK, USA; StatSoft, Krakow, Poland).

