## Figures and Tables

**Figure 1 ijerph-16-04841-f001:**
[figure not shown]
Sample collection chart.

**Table 1 ijerph-16-04841-t001:** Timetable of data collection.

Timing	Activities	Group	
		Experimental	Control
T0 visit (enrolment)	Eligibility screening; Written informed consent; Assignment to the experimental or control group.	✕	
T1 visit (baseline)	Data collection of diet quality and other lifestyle factors, quality of life, nutrition knowledge, sociodemographic factors.	✕	✕
	Measurements of adiposity, metabolic parameters, and thyroid function.	✕	✕
	Dietetic counseling.	QDP	CDC
Between visits	Home collection of dietary data with self-monitoring.	✕	
T2 visit (1-month follow-up)	Dietetic consultation to boost compliance with dietary guidelines.	✕	✕
	Data collection of diet quality and other lifestyle factors, quality of life.	✕	✕
	Measurements of adiposity and metabolic parameters.	✕	✕
Between visits	Home collection of dietary data with self monitoring.	✕	
T3 visit (6-month follow-up)	Data collection of diet quality and other lifestyle factors, quality of life, nutrition knowledge.	✕	✕
	Measurements of adiposity, metabolic parameters, and thyroid function.	✕	✕

QDP—a qualitative dietary protocol; CDC—conventional dietetic counseling.

**Table 2 ijerph-16-04841-t002:** Participant eligibility criteria. BMI: body mass index.

**Inclusion Criteria**: women age >18 and <60 years; prior diagnosed Hashimoto thyroiditis: hypothyroidism or subclinical hypothyroidism; medical certificate for levothyroxine treatment or other thyroid hormones; agreement to take part in the study;

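### Continuous outcomes are tested as unadjusted six-month change, although randomisation is stratified by age and baseline values are available as covariates

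*Protocol article*

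**What the plan says.** **Allocation.** Section 2.3 of the protocol article: "Stratified randomization will be based on age and will be carried out by a researcher not directly involved in the study". The number of age strata and their cut-points are not given. The Abstract gives equal allocation: "The subjects will be randomly allocated into the experimental/control groups (50/50)".

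**Measurements.** Table 1 schedules diet quality, quality of life (QoL), nutrition knowledge, adiposity, metabolic parameters and thyroid function at baseline (T1) and at six months (T3). Part of this is repeated at one month (T2): "Data collection of diet quality and other lifestyle factors, quality of life", together with adiposity and metabolic parameters. AdhS is the exception. Sections 1.2 and 2.4 derive it from diaries kept during follow-up by the experimental group alone, so it has neither a baseline value nor a control-arm value.

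**Analysis of continuous outcomes.** Section 2.12 sets out to compare the groups: "two-tailed tests will be applied; *p*-values < 0.05 will be considered significant". The quantity analysed is change from baseline at six months, by a dependent-samples t-test if normally distributed and a Mann–Whitney test if not. No covariate is named.

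**Regression.** Models appear only for categorised outcomes: "logistic regression modeling will be applied to determine the chance of the occurrence of high diet quality, high AdhS, high QoL", and likewise for adiposity and metabolic parameters. On adjustment: "A crude model and models with an adjustment for confounders will be created".

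**The concern.** Neither named test for continuous outcomes can carry a covariate. The factor used to balance the arms is then absent from the analysis, and the baseline value, usually the strongest predictor of the six-month value, is used only by subtraction. Subtraction fixes the coefficient of baseline at 1. A linear model estimates that coefficient and, in a randomised comparison, does at least as well.

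The same sentence has a second fault. A dependent-samples t-test asks whether an arm changed over time. It does not estimate the difference between arms on which Section 2.11 sizes the trial. The alternative offered for non-normal data, Mann–Whitney, is an independent-samples test, so the two are not counterparts. One adjusted linear model comparing the arms would settle both matters.

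At stake is precision in a trial that expects about 40 completers per arm, and a clear statement of the estimate that answers the main question.

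**Working it through.** **1. The plan's own figure.** Section 2.11 assumes, "in the experimental/control group, a decrease by 20/10 points and 2.0/1.0 kg/m^2^, respectively", so the arm differences are 20 − 10 = 10 points and 2.0 − 1.0 = 1.0 kg/m². It adds: "For this calculation, a 5% significance level and 80% power were considered". Baseline numbers per arm are 50 (QoL) and 42 (BMI), including 20% drop-out. No SD is stated, so these numbers cannot be reproduced; the SD can only be back-solved.

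From n = 2·SD²·(1.960 + 0.842)²/δ² it follows that SD = δ / [2.802·√(2/n)].

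- QoL: 50 × 0.8 = 40 evaluable per arm; SD = 10 / (2.802 × 0.2236) = 15.96 points.
- BMI: 42 × 0.8 = 33.6, giving SD = 1.46. Reading the inflation as 42/1.2 = 35 gives SD = 1.49 kg/m².

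Assumption: these are SDs of change, and a two-sample comparison of change has 80% power.

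**2. Baseline as a covariate instead of subtraction.** Let the variance be σ² at both visits and the correlation r. Per woman, the change score has variance 2σ²(1−r) and the baseline-adjusted residual has σ²(1−r²). The ratio is (1+r)/2, a reduction of (1−r)/2. Power is Φ(2.802/√ratio − 1.960).

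| r (assumed) | Ratio | Reduction | Power, QoL, 40 per arm | Evaluable per arm for 80% (40 × ratio) |
|---|---|---|---|---|
| 0.5 | 0.75 | 25% | 89.9% | 30 |
| 0.6 | 0.80 | 20% | 87.9% | 32 |
| 0.7 | 0.85 | 15% | 86.0% | 34 |
| 0.9 | 0.95 | 5% | 82.0% | 38 |

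**3. A plausible r for BMI.** From SD(change)² = 2σ²(1−r), r = 1 − SD(change)²/(2σ²). Take SD(change) = 1.49 and assume a baseline SD of 3 to 4 kg/m²:

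- σ = 3: r = 1 − 2.22/18 = 0.877; reduction (1 − 0.877)/2 = 6.2%.
- σ = 4: r = 1 − 2.22/32 = 0.931; reduction (1 − 0.931)/2 = 3.5%.

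For BMI the gain is therefore small.

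**4. Age.** If age correlates with the analysed outcome at ρ and the arms are balanced on age, adjustment multiplies the residual variance by 1 − ρ². For ρ from 0.1 to 0.4, power with age in the model is 80.4% to 86.4%. Without age, the true type I error of a nominal 5% test is 0.0489 to 0.0325, that is, below 5%.

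**The case against.** The strongest reply is that a between-arm comparison of change is unbiased under randomisation, so the preference for covariate adjustment concerns efficiency, not validity. That stands. It is also true that for BMI, one of the two sample-size outcomes, the gain may be only a few per cent.

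Several stronger readings are tempting, and the article does not support them.

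- *Baseline is ignored.* It is not: the analysed quantity is change from baseline. What is missing is baseline as a covariate. Quoting gains against a comparison of six-month values alone would also mislead, because the plan does not propose that analysis.
- *Every outcome can be baseline-adjusted.* AdhS cannot, and it allows no arm comparison.
- *Cutting the scores costs the trial its power.* With 40 per arm and the implied SD, a median cut would lower power from 80% to 59.8%, and a cut at the 30th or 70th percentile to 55.1%. But no median split is stated, the cut-offs that Sections 2.4, 2.9 and 2.10 give are fixed thresholds, and the logistic models accompany the continuous analysis.
- *Confounders will be picked after the data are seen.* Section 2.12 does not say how or when they are chosen, and age may be among them. The list may sit in the full protocol or analysis plan, as may an analysis of the T2 data. Neither absence is counted here.
- *Omitting the stratification factor invalidates the tests.* It makes them slightly conservative.

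**Conclusion.** The point holds as one of efficiency and clarity. As written, Section 2.12 leaves age out of the continuous analyses, uses baseline only by subtraction and, for normally distributed outcomes, names a test that does not compare the arms. Compared with a two-sample test of change, baseline adjustment would reduce the variance of the arm difference by 15% to 25% at r = 0.7 to 0.5, and by about 3.5% to 6% at the correlations plausible for BMI. Age alone would add 0.4 to 6.4 percentage points of power for ρ of 0.1 to 0.4.

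These sizes assume equal variances at the two visits, correlations that the article does not state, an SD back-solved from the stated numbers and, for BMI, an assumed baseline SD. The direction does not depend on the value of r: (1+r)/2 is below 1 whenever r is below 1. The change is worth making because it uses data already planned; the trial is not invalid without it.

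**What to change.** In Section 2.12, for each continuous outcome other than AdhS, make the main analysis a linear model of the six-month value with arm, age and the baseline value of the same measure. Report the arm difference with its 95% CI. State whether age enters as years or as the strata used at randomisation. Where T2 is measured (diet quality, QoL, adiposity, metabolic parameters), a mixed model of the T2 and T3 values with arm, visit, arm-by-visit, baseline and age is an option; nutrition knowledge and thyroid function have no T2 value and take the simpler model. Judge distributional assumptions on the residuals, with any transformation fixed beforehand.

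Call the logistic models on cut scores supportive, and fix their covariates in advance as arm, age and the baseline value of the same measure. Report AdhS, including its high category, descriptively within the experimental arm.

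The cost is wording and slightly more analysis work, with no new data. The one constraint is that the covariates must be fixed before outcome data are seen.

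### Randomisation is stratified by age, but the tests fixed for continuous outcomes cannot use age; if age is prognostic, a between-arm comparison is mildly conservative and forgoes some efficiency

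*Protocol article*

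**What the plan says.** - **Randomisation** (Protocol article, section 2.3): "Stratified randomization will be based on age". Age is the only factor named. The number of strata, the cut-points and the method of balancing within strata are not given.
- **Continuous outcomes** (section 2.12): changes from baseline to six months "will be verified with a T-test for dependent samples or a Mann–Whitney test", the choice depending on normality. The variables listed include the QoL scores and the markers of adiposity, and QoL and BMI are the outcomes on which section 2.11 sizes the trial.
- **Categorical outcomes** (section 2.12): logistic regression, of which the article says "A crude model and models with an adjustment for confounders will be created". The adjustment factors are not listed.
- **Sample size** (section 2.11): no gain from stratification is claimed.

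**The concern.** Stratified allocation with balance inside the strata takes age differences out of the contrast between arms. A test with no age term still counts those differences as random error in its standard error. If age is related to outcome, the standard error is then larger than the true sampling variation of the arm difference. The test rejects less often than its nominal 5%, and precision that the design makes available goes unused.

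For continuous outcomes this is not a covariate list that could simply be filled in elsewhere. The article names the tests, and neither has room for age. An analysis plan could use the strata only by replacing them. About 40 women per arm are expected to complete, so a gain in precision that needs no extra patients is worth having.

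**Working it through.** **Inputs from the article**
- Allocation: "experimental group (QDP; approximately n = 50) or the control group (CDC; approximately n = 50" (section 2.3).
- Error rates: "a 5% significance level and 80% power were considered" (section 2.11); "two-tailed tests will be applied" (section 2.12).
- Assumed mean changes, experimental/control: "a decrease by 20/10 points and 2.0/1.0 kg/m^2^, respectively" (section 2.11), so differences of 10 QoL points and 1.0 kg/m².
- Size: "50/50 for overall QoL and 42/42 for BMI), including a 20% drop-out rate at the end of the study" (section 2.11), so 50 × 0.8 = 40 completers per arm for QoL and 42 × 0.8 = 33.6 for BMI.

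**Input not in the article**
- R², the share of outcome variance explained by the age strata. It is assumed here and shown over a range.

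**Step 1. The plan's own figure.** No standard deviation is stated, so the sample size cannot be reproduced independently. Solving SD = difference / [(1.960 + 0.842) × √(2/n)] gives 10 / (2.802 × √(2/40)) = 15.96 for QoL and 1.0 / (2.802 × √(2/33.6)) = 1.46 for BMI. The stated numbers are attainable with such values. The results below do not depend on the SD, because they are set at the effect that gives 80% power without age.

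**Step 2. Formulas** (normal approximation, balance within strata)
- Excess of the unadjusted standard error: 1/√(1−R²) − 1
- True type I error of the unadjusted test: 2 × [1 − Φ(1.960/√(1−R²))]
- Power without age: Φ((2.802 − 1.960)/√(1−R²))
- Power with age strata in the model: Φ(2.802/√(1−R²) − 1.960)

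**Step 3. Results**

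| Assumed R² | SE too large by | True type I error, unadjusted | Power without age | Power with age | Forgone gain (points) |
|---|---|---|---|---|---|
| 0% | 0% | 5.0% | 80.0% | 80.0% | 0 |
| 2% | 1.0% | 4.8% | 80.24% | 80.79% | 0.6 |
| 5% | 2.6% | 4.4% | 80.61% | 81.97% | 1.4 |
| 10% | 5.4% | 3.9% | 81.25% | 83.97% | 2.7 |
| 20% | 11.8% | 2.8% | 82.66% | 87.95% | 5.3 |

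For R² = 10%: √0.9 = 0.9487; 0.842/0.9487 = 0.887, and Φ(0.887) = 81.25%; 2.802/0.9487 − 1.960 = 0.993, and Φ(0.993) = 83.97%.

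**Step 4. Check by simulation.** There were 20,000 trials per setting, with 40 per arm and two equal age strata balanced by design. An unadjusted two-sample t-test was compared with a linear model containing the stratum.

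| Assumed R² | Type I error, without v with stratum | Power, without v with stratum |
|---|---|---|
| 0% | 5.1% v 5.1% | 78.9% v 79.0% |
| 5% | 4.5% v 5.0% | 79.5% v 80.9% |
| 10% | 3.7% v 4.9% | 80.1% v 83.0% |
| 20% | 2.7% v 5.0% | 81.7% v 87.6% |

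The pattern agrees with the formulas. Simulated powers lie up to about one point lower, and do so at R² = 0 as well, so this comes from the normal approximation and not from age.

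**The case against.** **The effect may be close to nothing.** The article sizes and analyses changes from baseline, and a change removes stable differences between women, including age differences in level. At R² of 1% the standard error is only 0.5% too large and the gain 0.3 points; at 2%, 1% and 0.6 points. This stands. Choosing age as the stratification factor suggests that the investigators thought it might matter, but does not show that it does.

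**Balance within strata is assumed.** Section 2.3 does not describe the balancing method, and 20% drop-out may disturb balance. This stands as a condition on the figures.

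**The calculation is for a two-sample comparison of means.** The dependent-samples t-test in section 2.12 compares time points within an arm, so the question does not arise for it. That no between-arm test is named for normally distributed outcomes is a separate defect. The figures describe the unadjusted two-sample comparison that would take its place, and are only a guide for Mann–Whitney.

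**Four stronger readings are tempting, and the article does not support them.**
- A reader might infer that no between-arm analysis uses age. The adjusted logistic models may include it, since their factors are unnamed, and such a list may properly sit in an analysis plan that is not shown.
- A reader might infer that planned power is lost. Section 2.11 counts on no stratification gain, and power without age stays close to 80% throughout.
- A reader might carry the standard-error figures over to the odds-ratio intervals. They do not apply there: adding a prognostic stratum to a logistic model tends to raise the standard error of the arm log odds ratio while moving the estimate away from zero. In an illustrative simulation of 80 women with assumed log odds ratios of 0.8 for arm and 1.0 for stratum, the mean standard error was 0.46 crude and 0.48 adjusted.
- A reader might call the crude logistic model an error. Reporting it beside adjusted models is not one.

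**Conclusion.** The point holds as one of efficiency for the continuous outcomes. The design uses age, and the tests fixed for the outcomes on which the trial is sized cannot. If age predicts the six-month outcome and balance holds within strata, an unadjusted between-arm test is mildly conservative. The cost is negligible at R² of 2% or less and modest at 5–10% (1.4 to 2.7 points of power). It reaches about 5 points only at 20%. All R² values are assumptions. Nothing here biases the estimate or inflates type I error. For the logistic models the point is only that age is neither fixed nor excluded as an adjustment factor. The change is worth making because it is nearly free, not because the stated analysis would mislead.

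**What to change.** In section 2.12:

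1. Compare the arms on each continuous outcome with a linear model of the six-month value on arm, the T1 value of that outcome, and age stratum (or age). Where ranks are preferred, use a van Elteren test stratified by age.
2. Name the age stratum as a covariate in the adjusted logistic models. The crude model may remain as a secondary display.

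Item 1 would also supply the parametric between-arm comparison that the dependent-samples t-test does not give. Outcomes without a T1 value, such as the diary adherence score, are outside this model.

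The cost is a sentence or two of analysis text. Age is already recorded (section 2.8) and used at allocation, so no further patients, visits or measurements are needed.
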